**Fig. 1 Fig1:**
[figure not shown]
Information flow.  standard information flow  feedback information flow

To prevent false alarms during e.g. holidays or physical illness, patients can individually pause the monitoring of data during these episodes. For patients in the control group, no alarms will be forwarded to the respective study center. All patients receive guideline-based, state-of-the-art maintenance treatment for bipolar disorder. In addition, within the study protocol requirements the investigators aim at giving maximum flexibility to the study participants as to the required study appointments. To ensure patients adherence and continued data collection in both groups, an automated email is sent to the study center when no smartphone activity is monitored within 24 h. In case of continued non-adherence to study protocol, such as repeatedly deactivated smartphone for more than 24 h, patients can be excluded from further participation. To improve adherence, patients receive an expense allowance of 15 € per month to ensure that costs are covered for possible necessary adaptions of mobile plans. If using the study smartphone, patients can further keep the device once participation is completed following study protocol so that changing back to another device after study participation is excluded as a recruitment hindrance. All patients can withdraw previously provided consent at any time without specification of reasons and without any adverse or disadvantageous consequences.

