### Intervention

All patients included in this study use a smartphone with an installed application called movisensXS. MovisensXS is an electronic e-diary software, which additionally can track and transmit smartphone data collected from sensors inside the device. Patients can decide, whether they want to use the study smartphone (a currently available mid-priced Samsung smartphone) or install the app via Google Play Store on their own device. Technical requirements include Android version 4.0 or higher, CPU of 600 MHz or above, acceleration sensor and GPS. In this study, the movisensXS app monitors current location via GPS, an estimate of the covered steps (using the devices’ acceleration sensor), mobile communication parameters (number and duration of incoming and outgoing calls, number and length of incoming and outgoing text messages, number of different call and text contacts), usage duration of common communication apps (e.g. WhatsApp, Facebook Messenger), number and duration of times the display of the device is on/off, as well as rates of transmitted and received data. For enrolled patients, a pseudonymized electronic file is created on the movisensXS platform and all data is transmitted daily to a secured server. Data protection requirements are complied with at any stage of data storage and transmission processes. Every 24 h data are drawn from the data storage server by a feedback server via a secure connection and data of patients in the intervention group are compared with individual baseline data performed. The intervention-algorithm is based on a combination of threshold values associated with parameters which are linked to DSM-5 criteria of bipolar disorders, i.e. change in goal-directed or non-goal directed activity and change of communication pattern (e.g. more talkative than usual). Psychomotor agitation/retardation is operationalized by movement patterns derived from two smartphone sensor systems. Daily travel distances in kilometers per day are calculated via GPS coordinates. The acceleration sensor in the smartphone tracks acceleration in three spaces. Daily movement activity is assessed by number of steps. General inactivity is calculated by numbers of hours without any smartphone activity, which includes no acceleration data, no phone calls or text messages and the smartphones display being turned off. Communication is operationalized by tracking the frequency and length of phone calls and text messages using the smartphone.

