First, daily values are calculated for all monitored parameters. During a stabilization period (four weeks of euthymia) in the prerandomization phase individual baseline values (mean and standard deviation) for the persons’ typical smartphone usage, communication and activity behavior in the following eight parameters are calculated: (1) travelled distance (km/day), (2) steps/day, (3) number of outgoing calls/day, (4) average phone call duration/day, (5) length of outgoing text messages/day, (6) hours when smartphone is inactive, (7) frequency of display on/day and (8) duration of display on/day. During the intervention phase daily deviations of daily values from baseline are calculated. A defined alarm threshold is exceeded when two or more parameters exceed or fall below the 20% or above the 80% percentile on three subsequent days. The direction of the deviation has to be the same for each variable on these three days but can differ between different variables. For patients in the intervention group, alarms are automatically forwarded by email to the respective study center. The attending psychiatrist contacts the patient and decides whether an affective episode is present or developing and carries out the next standard procedures as in usual practice, e.g. appointing a personal contact to discuss treatment options with the patient. If no affective episode is present and the alarm is not explicable by current external circumstances of the patients’ situation the signal is rated as a false alarm. In this case, the alarm thresholds are raised by 5% (values of the 20% and the 80% percentile). In case of an undetected mood episode during the intervention phase the thresholds will be lowered by 10%. Information flow is depicted in Fig. 1.

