### Statistical analysis

#### Confirmatory analysis

The primary objective (i.e. comparison of time to a new episode under SBAA+ vs SBAA) will be addressed with survival analysis. Kaplan-Meier plots will be used for estimating the survival functions; a Log-Rank test will be used to formally compare time to a new episode across treatment groups. By using this strategy, the analysis will include data from all patients who were randomized (ITT analysis). Although randomization will be used to attain comparable conditions at baseline in both groups, imbalances with respect to major confounders cannot be completely ruled out. In this case, the predefined survival analyses will be backed up by a Cox-regression which includes these confounders. All patients who have been randomized will be included in the statistical analyses.

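### Excluding randomised patients for phone non-adherence may end outcome follow-up for a reason linked to relapse, which risks informative censoring

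*Protocol article*

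**What the plan says.** The rule is in the protocol article under Methods/design, Intervention, in the paragraph after Fig. 1. In case of continued non-adherence, with a phone switched off repeatedly for over 24 h as the example, "patients can be excluded from further participation". The same paragraph says that in both groups "an automated email is sent to the study center when no smartphone activity is monitored within 24 h".

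The Intervention section also uses a silent phone as a signal. "General inactivity is calculated by numbers of hours without any smartphone activity", meaning no acceleration data, no calls or texts, and the display off. The sixth of the eight parameters feeding the alarm is listed as "6) hours when smartphone is inactive".

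Under Outcomes, the primary endpoint is determined by SCID I section A at monthly assessments. Under Randomization and blinding, raters are blinded, while patients and study psychiatrists know the allocation. Under Confirmatory analysis, "a Log-Rank test will be used to formally compare time to a new episode across treatment groups", and "All patients who have been randomized will be included in the statistical analyses".

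The article does not say whether ratings continue after an exclusion.

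**The concern.** An exclusion from further participation most naturally ends the monthly ratings as well. In a time-to-event analysis the patient would then be censored at that date. Kaplan-Meier estimation and the log-rank test assume that patients censored at a given time have the same future risk as those still followed. Here the ground for removal overlaps with a pattern that the trial itself monitors as a possible sign of an episode, so the assumption is doubtful on the trial's own rationale.

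The rule could also work differently in the two arms. It is optional, the study psychiatrists are unblinded, and only in SBAA+ does an alarm lead to contact with the patient. If impending episodes go unrecorded more often in one arm, the estimated hazard ratio is biased. If they go unrecorded equally often, events and power are lost and both survival curves look too favourable.

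**Working it through.** **Reproducing the stated power.** Inputs from Sample size calculation: 60 per group, control hazard 0.06 per month, hazard ratio 0.5 (so 0.03 in SBAA+), drop-out 2.5% (read as monthly, d = 0.025), one-sided α = 0.05. Follow-up is 18 months (Randomization and blinding).

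Expected events per arm = 60 × λ/(λ+d) × (1 − exp(−18(λ+d))):
- SBAA: 60 × 0.06/0.085 × (1 − e^−1.53) = 60 × 0.553 = 33.2
- SBAA+: 60 × 0.03/0.055 × (1 − e^−0.99) = 60 × 0.343 = 20.6
- Total: about 53.7

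Schoenfeld power = Φ(√53.7/2 × ln 2 − 1.645) = Φ(0.90) = 81.5%, against 81% stated. Replacing λ by d in the numerator gives drop-out before relapse of 23.0% (SBAA) and 28.6% (SBAA+). The mean is 25.8%, which matches the stated 26%. No stated figure is wrong because of the exclusion rule.

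**Effect of the rule, if exclusion ends follow-up.** The share f of first episodes lost this way is not in the document, so a range is assumed. To first order, losing a fraction f of events in one arm multiplies that arm's observed hazard by (1 − f):
- True HR 1.0, loss in SBAA+ only: 1.0 × 0.9 = 0.90; 1.0 × 0.8 = 0.80
- True HR 0.50, loss in SBAA only: 0.50/0.9 = 0.56; 0.50/0.8 = 0.63

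A log-rank simulation used the same hazards, with 4,000 runs per scenario. A share f of patients with an observed event was instead censored about one week before it. The apparent HR is a one-step log-rank estimate.

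| True HR | f in SBAA | f in SBAA+ | Patients affected | Apparent HR | One-sided rejection rate |
|---|---|---|---|---|---|
| 1.0 | 0 | 0 | 0 | 1.00 | 4.8% |
| 1.0 | 0 | 10% | 3.4 | 0.90 | 10.6% |
| 1.0 | 0 | 20% | 6.7 | 0.80 | 22.3% |
| 1.0 | 10% | 0 | 3.3 | 1.12 | 1.6% |
| 0.5 | 0 | 0 | 0 | 0.50 | 81.6% |
| 0.5 | 10% | 0 | 3.3 | 0.55 | 67.0% |
| 0.5 | 20% | 0 | 6.5 | 0.62 | 49.6% |
| 0.5 | 0 | 10% | 2.0 | 0.45 | 88.0% |
| 0.5 | 10% | 10% | 5.4 | 0.50 | 76.9% |
| 0.5 | 20% | 20% | 10.7 | 0.49 | 73.5% |

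With true HR 1.0 the rejection rate is the type I error; with 0.5 it is the power. The simulation error of a rejection rate is at most √(0.5 × 0.5/4000) = 0.8 percentage points. With true HR 1.0 and equal loss of 10% or 20%, the rejection rate stays at 5.0% and 5.6% and the apparent HR at 1.00 and 0.99.

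The hazard ratio is therefore sensitive to a few patients if the loss is one-sided, and hardly at all if it is equal.

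**The case against.** A reader might infer that the rule breaks the intention-to-treat analysis. The document does not support that. Confirmatory analysis keeps every randomised patient in the analysis, and the rule removes patients from participation, not from the analysis set. What is at risk is complete follow-up that does not depend on adherence.

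A reader might also take it as stated that excluded patients are censored and that unblinded staff decide. Neither is stated. The article gives no censoring rule and does not name who decides, and such detail may be in a full protocol or analysis plan that is not shown. Both remain inferences, though the first is the natural reading of the sentence.

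The trigger is not identical to the warning sign. The example is a phone repeatedly deactivated, as a case of continued non-adherence. An alarm needs at least two parameters deviating on three subsequent days. Patients may pause monitoring for holidays or illness, and a phone can be off for reasons unrelated to mood. But a phone that is off shows none of the activity whose absence defines inactivity, so the overlap is real.

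Finally, it is tempting to read the planned drop-out, about 31 of 120 patients (60 × 0.230 + 60 × 0.286), as the scale of the problem. That figure covers drop-out from all causes, is already in the power calculation, and is nowhere attributed to this rule.

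**Conclusion.** The concern holds as a risk of informative censoring created by an explicit but optional rule applied after randomisation. It rests on two readings: that exclusion ends the ratings, and that a phone left off may be related to an approaching episode. Bias in the hazard ratio needs a third condition, that exclusions differ by arm. The design makes this plausible but the document does not show it, and neither frequency nor direction can be derived from it.

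The figures for 10–20% loss illustrate sensitivity and are not predictions. One-sided loss of about 3 to 7 patients' episodes is enough to double or quadruple the type I error (loss in SBAA+), or to take power from about 81% to 67–50% (loss in SBAA). Because episodes that were never rated cannot be recovered at analysis, the sentence is worth changing even though the frequency is unknown.

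**What to change.** Reword the sentence so that continued smartphone non-adherence ends only data capture and alarms. The scheduled monthly blinded SCID, YMRS and IDS-C30 ratings continue to week 72 unless consent is withdrawn, and episodes after app discontinuation count in the primary analysis.

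Report app discontinuations and exclusions by arm, with timing and reason. Add a sensitivity analysis for censoring at exclusion, for example with each exclusion counted as an event.

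The cost is a short amendment. The ratings are already scheduled for every randomised patient. Some follow-up will be off-app, which slightly dilutes the contrast between arms. If remote rating is allowed in order to keep these patients, the option must be the same in both arms and the mode recorded: under Diagnostic and rating scales the SCID is described as face-to-face (for the screening diagnosis), and a change of mode confined to non-adherent patients could itself affect how episodes are rated.

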### Measures

#### Diagnostic and rating scales

At screening, bipolar diagnosis is assessed with the Structured Clinical Interview for DSM Disorders (SCID-I, German version) [25] for DSM-IV. An additional question concerning abnormally and persistently increased activity or energy is included to conform to current DSM-5 criteria for depressive, manic or hypomanic episodes [26]. The semi-structured interview is conducted face-to-face and is established for diagnosing mental disorders. Throughout the study, current affective episodes are assessed with the SCID-I section A for affective episodes, including the additional DSM-5 criterion described above. Furthermore, (hypo) manic symptoms are dimensionally rated with the Young Mania Rating Scale (YMRS) [27] which consists of 11 items. Symptom severity is rated with 0 to 4 points; four items are double-weighted. A total value below 12 is considered clinically insignificant. The YMRS is regarded as gold standard in mania psychometry and its reliability (*r* = .93) and validity (*r* = .86 to .89) are well studied [27]. Depressive symptoms are dimensionally rated with the Inventory of Depressive Symptomatology, clinician version (IDS-C 30) [28] which consists of 30 items. Symptom severity is rated with 0 to 3 points. A total value below 18 is considered clinically insignificant. The IDS is well established in the assessment of depressive symptom severity. Good reliability (*r* = .89) and validity (*r* = .81) are reported for patients with bipolar disorder [29]. All ratings will be performed by trained and experienced psychologists and/or psychiatrists and data is directly entered in the electronic database. In addition, source data are documented by paper and pencil and signed by the investigator upon completion. Paper versions of all instruments used are provided in the investigator site file in case a direct entry of data should not be possible due to technical reasons.

#### Outcomes

Primary outcome of this trial is time to new affective episode, defined by DSM-5 criteria for depressive, manic or hypomanic episode. The primary outcome will be determined by SCID I section A (for DSM-IV, additional DSM-5 question for energy/activity being included), criteria for current depressive and (hypo) manic episode, in monthly assessments during the intervention phase. The primary outcome is clinically highly relevant to determine the affective and mental stability of bipolar patients.

Secondary endpoints are (1) time to a new depressive episode, (2) time to a new (hypo) manic episode, (3) time to a new affective episode defined by DSM-5 but with modified time criterion of ≥ four days of episode duration, (4) percentage of assessments during intervention phase at which the original DSM-5 criteria for an affective episode are met, (5) percentage of assessments during intervention phase at which the modified DSM-5 criteria for an affective episode are met. These outcomes will also be determined by SCID I section A (for DSM-IV, additional DSM-5 question for energy/activity being included), criteria for current depressive and (hypo) manic episode, in monthly assessments during the intervention phase. Further secondary outcomes are (6) percentage of assessments during intervention phase at which criteria for an affective episode, defined by YMRS (> 12) and IDS-30 (> 18) score are met and (7) average severity of manic and depressive symptoms at assessments during intervention phase. These criteria are estimated by total YMRS and IDS-C30 scores at every assessment. Operationalization of the secondary outcomes (8) percentage of assessments during intervention phase at which the patient was hospitalized for an affective episode, and (9) percentage of days during intervention phase at which the patient was hospitalized for an affective episode, is self-explanatory. (10) Number of adverse events is measured by the SAE (serious adverse event) reporting form included in the electronic case report form (eCRF).

The outcome measures chosen in our trial are commonly used in similar long-term treatment trials in bipolar disorders. In particular our primary endpoint, time to new episode, is the most established endpoint in new approval-seeking trials for psychopharmacological drugs in long-term treatment of bipolar disorders. In addition, our secondary endpoints will allow a better insight in the robustness of our primary endpoint and in developing an understanding of the economic impact of our intervention.

### Study procedure

Inpatients and outpatients with bipolar disorder I/II (currently symptomatic or stable) are assessed for eligibility by experienced clinical staff working at the study site who will present all relevant information about the background, design, procedure, etc. of the study to the patient and obtain informed consent in case of given eligibility. After having signed informed consent, a pseudonymized file is created for the patient in the electronic database and the movisensXS smartphone application is installed on a study smartphone handed over to the patient for his or her time of study participation, or, if wished, on the patient’s own device. Participants continuously receive open, guideline-based treatment for potential current (hypo)manic and depressive symptomatology for up to 20 weeks at the study sites outpatient clinics. As soon as stabilisation criteria are met (Young Mania Rating Scale total score < 12 and Inventory of Depressive Symptomatology, clinician version total score < 18) during four consecutive weeks, a baseline of the persons individual smartphone usage pattern during euthymia is automatically defined. Having fulfilled randomization criteria (four consecutive weeks with YMRS total score < 12 and IDS-C30 total score < 18), patients are randomly assigned to the Smartphone-Based Ambulatory Assessment group, including real-time data capture and data-driven therapeutic interventions (SBAA+), or to the Smartphone-Based Ambulatory Assessment group, only including real-time data capture (SBAA).

### Randomization and blinding

A randomization list is stored in the electronic database where all collected data is entered using eCRFs. Based on this list, patients are allocated to the two groups (SBAA resp. SBAA+) by block randomization, stratified by age and type of bipolar disorder (I or II) for every study site. Pseudonymized files are created in the database for enrolled patients. The system allocates patients to the groups corresponding to the stored algorithm for randomization and the required stratification factors. The patient and the assigned psychiatrist are automatically and instantly informed about which group (SBAA vs. SBAA+) the patient was allocated to once randomization is carried out via the database system. As regular ratings must not be biased by group allocation knowledge, the observer/rater remains blinded. Both treating psychiatrist and patient are asked explicitly not to disclose any information allowing conclusions regarding group allocation. As the study psychiatrists are not blinded, there was no need to provide special procedures for emergency unblinding.

The intervention phase is planned for 18 months (72 weeks). During this time, state-of-the-art treatment of the bipolar condition continues for both groups. Attending psychiatrists will receive automatic feedback from the movisensXS feedback server, every time the previously calculated individual thresholds of patients in the SBAA+ group are significantly exceeded in any direction. A standardized procedure follows, where the psychiatrist contacts the patient to assess, whether (a) the changes in smartphone usage patterns can be explained by external circumstances, or (b) show no hint for the beginning of a new affective episode (false alarm), or (c) the changes result from early signs of bipolar episodes. In this case treatment options are discussed with the patient as in regular guideline-based treatment. Additionally, in the case that the rater detects an affective episode, the study clinician will be informed so that thresholds can be changed towards more sensitivity if the patient is enrolled in the intervention group and no automatic alarm has been present.

On a monthly base, assessments of bipolar psychopathology (SCID, YMRS, IDS-C30) are conducted by the rater who is blind to the patients’ group assignment. A post-trial follow-up of four weeks per patient follows subsequently after the end of the 72 weeks intervention phase. Figure 2 shows the schematic study flow, serving as a detailed overview for the time schedule of enrolment, intervention, assessment and visits for the participants.

**Fig. 2 Fig2:**
[figure not shown]
Study flow

The study population participants should be recruited during 18 months, the first patient was enrolled in January 2017.

### Statistical analysis

#### Confirmatory analysis

The primary objective (i.e. comparison of time to a new episode under SBAA+ vs SBAA) will be addressed with survival analysis. Kaplan-Meier plots will be used for estimating the survival functions; a Log-Rank test will be used to formally compare time to a new episode across treatment groups. By using this strategy, the analysis will include data from all patients who were randomized (ITT analysis). Although randomization will be used to attain comparable conditions at baseline in both groups, imbalances with respect to major confounders cannot be completely ruled out. In this case, the predefined survival analyses will be backed up by a Cox-regression which includes these confounders. All patients who have been randomized will be included in the statistical analyses.

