## Methods/design

### Design and study setting

This study is a randomized, multi-center, rater-blinded, active-control, parallel group trial within a nationwide research project on the topic of innovative methods for diagnostics, prevention and interventions of bipolar disorders [23, 24]. Assessments are scheduled weekly in the prerandomization phase (4–20 weeks) and monthly in the intervention phase (72 weeks). End of intervention phase is followed by a post-intervention visit after four weeks. Five outpatient centers of psychiatric clinics at German university hospitals (Dresden, Berlin, Hamburg-Eppendorf, Frankfurt, Bochum), specialized in the treatment of bipolar disorders will assess data for this trial. Recruitment shortages are planned to be overcome by opening further study sites (Neuruppin, München, Tübingen). The coordinating site is the University Medical Center in Dresden, supported by the Coordination Center for Clinical Trials (KKS). The clinical trial conforms to the requirements of the MDR (Medical Device Regulation).

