#### Explorative analysis

Regarding secondary endpoints, separate survival analyses will be applied according to the variables level of measurement. For continuous endpoints, means and standard deviations respectively medians and quartiles are applied (graphically according to confidence intervals respectively boxplots), for categorical endpoints absolute and relative frequency are applied. Depending on the distribution of the analyzed variables, a *t*-test, *U*-test and *Chi*^2^-test are applied. For intraindividual comparisons a paired *t*-test is applied for normally distributed variables, and a Wilcoxon-test for not normally distributed variables.

Access to the final trial dataset is granted to the sponsor who is the owner of all data. Access is also granted to biometry staff.

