### Sample size calculation

Required sample size was calculated as in: *n* = 360 to be assessed for eligibility; *n* = 180 to be allocated to trial; *n* = 120 to be randomised to SBAA+ or SBAA; *n* = 120 to be analysed. The sample size of *n* = 60 per group was based on a power calculation for survival analysis with constant hazard and drop-out rates. This power calculation requires specific assumptions regarding (a) drop-out rate in SBAA (placebo), (b) global drop-out rate and (c) hazard ratio. Drop-out rate in SBAA (Placebo) was calculated with data from the psychiatric outpatient clinic, as this population most closely corresponds to the examined sample. Accordingly we expect a monthly hazard rate of 6%, which is equivalent to a relapse rate of 62% for the course of the trial. From our experience with comparable patients in similar studies we expect a drop-out rate of approximately 2.5%. This is equivalent to a drop-out rate of 26% for the course of the trial. A hazard ratio of 0.5 is estimated, according to a reduction of the relapse rate from 62 to 41% in the intervention group. This assumption is consistent with results of a Cochrane review on interventions, helping patients to identify early warning signs. The hazard ratio of 0.5 equals the median hazard ratio in studies, which compare TAU and TAU plus detection of EWS for relapse. This estimation is considered rather conservative as smartphone usage in this trial expectedly leads to a quicker and more reliable detection of warning signs, thus we expect a greater effect compared to the studies mentioned. Hence, with 81% this trial is sufficiently powered to demonstrate the advantage of SBAA+ compared to SBAA regarding the primary outcome (α = .05, one-tailed). Power calculation was performed using SAS software, version 9.3 (2011, Cary, NC).

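### Randomisation is stratified by age, bipolar type and site, but the confirmatory log-rank test is described without these factors and adjustment waits for an observed imbalance, which is the wrong criterion and can cost power

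*Protocol article*

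**What the plan says.** Under Randomization and blinding, patients are allocated "by block randomization, stratified by age and type of bipolar disorder (I or II) for every study site". Design and study setting plans "Five outpatient centers of psychiatric clinics at German university hospitals" and names three further sites to be opened if recruitment falls short.

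Under Confirmatory analysis, "a Log-Rank test will be used to formally compare time to a new episode across treatment groups". No strata or covariates are mentioned for this test. The section then notes that "imbalances with respect to major confounders cannot be completely ruled out" and continues: "In this case, the predefined survival analyses will be backed up by a Cox-regression which includes these confounders". It names no confounder and gives no criterion for imbalance, and the stratification factors are not said to enter any model.

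Under Sample size calculation, "The sample size of *n* = 60 per group was based on a power calculation for survival analysis with constant hazard and drop-out rates". The resulting power is given as 81% at a one-sided 5% level with a hazard ratio of 0.5.

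**The concern.** The sponsor chose age, bipolar type and site as the factors worth controlling at allocation, but the stated analysis makes no use of them. Two things follow.

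First, if these factors predict time to relapse, leaving them out pulls the hazard ratio towards 1 and makes the test conservative, even when the arms are perfectly balanced on them. With about 54 expected events and a planned power of 81%, the trial has little to spare.

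Second, the stated rule adjusts for whatever is found imbalanced. Stratified blocks hold the design factors near balance, so the trigger will mostly pick up chance differences in other variables. The reason to adjust is prognostic strength, known or presumed in advance, and not the imbalance observed. A model whose existence and covariates depend on the data is also weak support for the primary result, because it can be run or left out, and filled, after the data are seen.

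**Working it through.** **1. Reproducing the stated power.** Inputs from Sample size calculation: 60 per group, control hazard 0.06 per month, hazard ratio 0.5 (so 0.03 per month under SBAA+), drop-out 2.5% taken as monthly, one-sided 5%. Follow-up is 18 months. With exponential event and drop-out times, the expected number of events is

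60 × [0.06/0.085 × (1 − exp(−0.085 × 18)) + 0.03/0.055 × (1 − exp(−0.055 × 18))] = 60 × (0.553 + 0.343) = 53.7.

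Schoenfeld's formula gives power = Φ(√53.7 × ln 2 / 2 − 1.645) = 81.5%. Reading the article's 62% and 26% as 18-month cumulative risks gives 81.0%, and taking 72 weeks as 16.56 months gives 80.1%. The stated 81% is therefore right for a log-rank test without strata under the plan's own assumptions.

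**2. What happens if the factors are prognostic.** Trials of 120 patients were simulated with the inputs above and stratified block randomisation. The following are assumptions not given in the article: 5 equally likely sites, 2 age classes, 35% bipolar II, blocks of 4, and all prognostic strengths. The settings are:
- none
- modest: hazard ratio 1.5 for type and 1.3 for age, site SD 0.2 on the log-hazard scale
- moderate: 2, 1.5 and 0.4
- strong: 3, 2 and 0.5

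Power (%) at a treatment hazard ratio of 0.5:

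| Setting | Log-rank, no factors | Cox, treatment only | Cox + type + age | Cox + type + age + site | Log-rank, every cell a stratum |
|---|---|---|---|---|---|
| None | 81.2 | 80.1 | 79.9 | 80.8 | 75.0 |
| Modest | 79.7 | 79.0 | 79.4 | 80.9 | 74.8 |
| Moderate | 75.7 | 74.8 | 78.4 | 81.0 | 74.1 |
| Strong | 70.6 | 70.8 | 77.2 | 81.8 | 73.1 |

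Monte Carlo error is about 0.6 to 1 point. The gap between the treatment-only and fully adjusted Cox models is 0.7, 1.9, 6.2 and 11.0 points. A second simulation with score tests (6000 trials per setting, with closely similar assumed strengths) gave gaps of 0.6, 2.1, 4.9 and 10.7 points.

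**3. Type I error at nominal 5%, Cox models, same order of settings.**
- Treatment only: 4.5, 4.8, 4.4 and 3.6%. The log-rank test without factors likewise falls, from 5.6% to 3.8%.
- Type and age: 4.7, 5.2, 5.4 and 4.8%.
- Type, age and site as fixed covariates: 5.6, 5.8, 5.8 and 5.5%. Other runs at 5 sites ranged from 5.0 to 6.2%, with no clear benefit from a score or likelihood-ratio test. At 8 sites, score tests reached up to 6.8%.
- Type and age with site as a Cox stratum, 5 sites: 5.2 to 5.3%.

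**4. Why not stratify the log-rank test on everything.** Five sites × 2 types × 2 age classes make 20 cells, or 120/20 = 6 patients each. Power drops to about 75%. With 8 sites there are 32 cells (120/32 = 3.75 patients each), and power is 69.8% under modest effects.

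**The case against.** The strongest reply is that this is a condensed article. It never calls the log-rank test unstratified, and an analysis plan not shown here may stratify it or name the covariates. That stands as far as the silence goes. It does not cover the adjustment rule, which the article states positively: a Cox model if imbalance appears, with the imbalanced confounders. An analysis plan that pre-named the covariates would depart from that rule.

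Three further objections stand in part.
- The power loss depends on prognostic strengths that the article does not give. With none to modest effects it is negligible.
- Full adjustment with site as fixed covariates runs slightly above the nominal level while the unadjusted test runs below it, so part of the 5 to 11 points is a difference in size. Adjusting for type and age alone keeps size near 5% and gains 78.4 − 74.8 = 3.6 points in the moderate setting and 77.2 − 70.8 = 6.4 in the strong one.
- The log-rank test is a valid confirmatory test as it is.

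A reader might infer that letting the data choose covariates inflates the confirmatory error rate. It does not: the log-rank test is predefined, the Cox model only backs it up, and ignoring prognostic strata makes the primary test conservative. A reader might also extend the point to the secondary endpoints. Those tests are labelled explorative and are valid under randomisation, so a different model there would be a preference.

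**Conclusion.** The point holds in a limited form. The plan stratifies on factors that its stated analysis does not use, and ties adjustment to observed imbalance, which is the wrong criterion. The consequence is a possible loss of power: about 0 to 2 points with no to modest prognostic effects and about 5 to 11 points with moderate to strong effects, against adjustment for type, age and site. These figures rest on assumed strengths, two age classes, 35% bipolar II, five equal sites and blocks of 4.

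It would go too far to say that the trial is underpowered or that the 81% is wrong. That figure reproduces for the test described, and nothing in the article shows how prognostic the factors are. The data-dependent choice of covariates weakens only the supporting model.

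**What to change.** In Confirmatory analysis, delete the imbalance trigger. Before unblinding, pre-name a Cox model with treatment, bipolar type and the age grouping used in randomisation, tested by a score test. Make it the primary test or, at minimum, a supporting analysis that is run whatever the baseline table shows. Keep the Kaplan-Meier curves and the unstratified log-rank test alongside it.

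If site is included, enter it as a Cox stratum and not as fixed covariates. The size of the site-stratified model was checked for 5 sites only, so it should be rechecked if the further sites open. Do not use a log-rank test stratified on every combination of site, type and age.

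The cost is a change of wording. If the factors turn out irrelevant, adjusting for type and age costs nothing measurable (about 81.5% power against 81.6% unadjusted), and adding site as a stratum costs about 1 to 2 points. The price of leaving site out is that type and age alone recover only part of the power available when site effects are large.
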